#### Study Procedures

##### Overview

This study uses a randomized double crossover clinical trial to evaluate a carbon fiber prosthetic foot with a frontal plane–adaptable linkage in two configurations: (1) unlocked, allowing frontal plane motion, and (2) locked, restricting frontal plane motion. When locked, the foot functions comparably to a conventional energy-storing-and-returning carbon fiber foot. A secondary aim is to compare the unlocked configuration to the participant’s usual prosthetic foot, representing the current standard of care.

The study follows an A1-B1-B2-A2 crossover design:

A conditions involve the use of the participant’s usual prosthetic foot.B conditions involve the study foot with the linkage either locked or unlocked. The order of the B conditions is randomized using block randomization stratified by study site.

A custom-designed pin system is used to lock the linkage and prevent frontal plane motion when required.

##### A1 (Baseline)

At the initial visit, participants provide demographic information and complete baseline questionnaires and performance assessments. They are then trained on online data entry procedures and fitted with the study prosthesis (either locked or unlocked, depending on randomization) by a licensed prosthetist. Participants with bilateral amputations receive matched prostheses. Once fitted with the study prosthesis, participants start the 2-week accommodation period.

##### B1 (First Intervention Phase)

Participants use the first randomized configuration of the study foot for two weeks during routine community activities. Throughout this phase, they submit usage data, subjective performance ratings, and qualitative feedback via an online logbook. At the end of B1, standardized questionnaires and performance assessments are administered.

##### B2 (Second Intervention Phase)

The frontal plane linkage is adjusted to the alternate configuration (locked or unlocked), and participants continue regular use of the study prosthesis for another two weeks. Data collection procedures mirror those in B1. This phase concludes with standardized assessments and a semistructured interview to compare experiences with both foot configurations.

##### A2 (Postintervention Reflection)

Participants return to using their usual prosthetic foot for two weeks. This phase is intended to facilitate reflection on the differences between the study prosthesis (particularly in its unlocked configuration) and standard care. At the final visit, participants complete additional questionnaires and a concluding semistructured interview.

### Outcome Measures

#### Physical Performance Measures

To determine if the META Arc novel prosthetic foot frontal plane motion improves mobility, participants will be assessed with the 10-meter Walk Test [5], Timed Up and Go (TUG) [5,6], the Three Times Figure-of-Eight Walk Test (3XF8W) [7], and the Four Square Step Test [8]. In addition to the typical timed outcome of these clinically based tests, additional spatiotemporal parameters will be measured with the Zeno electronic walkway (Figure 2). Spatiotemporal parameters of gait are believed to be functionally important and may be correlated with falls [9] and corroborate benefits of increased prosthetic ankle range of motion [10]. These secondary outcomes are hypothesis-generating for this population in relation to any changes in perceived function. These secondary outcomes will include the component TUG test [11] (Figure 3) and an instrumented four square test [12].

**Figure 2. F2:**
[figure not shown]
Component Timed Up and Go in the lab setting.

**Figure 3. F3:**
[figure not shown]
Timed Up and Go footfall patterns from the ProtoKinectics Movement Analysis Software (Zenometrics LLC).

#### Participant Qualitative Measures

The participant-related outcome measures include a demographic questionnaire and the Prosthetic Limb Users Survey of Mobility (PLUS-M). The PLUS-M is a 12-item questionnaire developed at the University of Washington Center for Outcomes Research in Rehabilitation, which examines typical everyday mobility activities on a 5-point Likert scale. Participants were also asked to fill out a logbook every day during the study. They could complete the logbook on paper or via a digital reminder system sent via email by REDCap.

Semistructured interviews will be completed during research phases B2 (investigational foot) and A2 (usual foot). These interviews will clarify significant events documented in the logbooks. The focus of interviews will be on gathering information about the participants’ experience using different prosthetic feet, with an emphasis on identifying activities that are facilitated or hindered by the functioning of the prosthetic foot.

### Statistical Analysis

The primary analysis will compare the META Arc foot in locked versus unlocked configurations. Statisticians will remain blinded to condition labels, analyzing outcomes as Condition X versus Y, with knowledge of the order (X→Y or Y→X), but not which corresponds to locked or unlocked.

Descriptive statistics (means and SDs for continuous variables; counts and percentages for categorical variables) will be used to summarize participant characteristics, stratified by amputation group. All analyses will be performed separately for each group.

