## Abstract

**Background:**

The primary objective of this study is to investigate whether a novel prosthetic foot with a polycentric ankle, which offers side-to-side adaptability, improves mobility and daily performance in individuals with (1) unilateral above-knee amputation, (2) unilateral below-knee amputation with a lower mobility level (K2) , or (3) bilateral amputation, any level of amputation. Traditional prostheses are primarily designed for forward walking and lack adaptability for navigating uneven terrain, turning, and executing other multidirectional tasks, often resulting in pain, instability, and limited function.

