**Objective:**

The objective of this testing protocol is to better understand the functional impact of a novel foot design that offers more inversion/eversion rotation of the polycentric ankle. Although the foot has the potential to address mobility challenges, it is unknown whether people with different amputations and mobility levels respond differently.

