**Methods:**

The study includes community-based mobility assessments, standardized questionnaires, and participant feedback. Although side-to-side adaptability prosthetic feet have shown benefits for highly active users, this study aims to evaluate the impact on individuals with more significant mobility limitations.

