### Primary Outcomes

Primary performance outcomes include the TUG, the 3XF8W, and the Four Square Step Test. Assumptions of normality and homogeneity will be tested. If met, a multivariate analysis of variance (MANOVA) will be used to evaluate the effect of foot configuration at α=.05. A permutational MANOVA will be used if assumptions are violated. If multivariate differences are significant, post hoc paired *t* tests (or Wilcoxon signed-rank tests if nonnormality is present) will be used to assess individual outcomes without correction for multiple comparisons. In order to help control the familywise type I error risk, pairwise comparisons of the primary outcomes will only occur if the multivariate difference comparison from the MANOVA is significant.

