### Power

With n=30 for the above-knee and K2 groups, the study is powered (>80%) to detect a standardized effect size of 0.53. In the bilateral group (n=16), the power is greater than 50% for the same effect size. Preliminary data show larger effects (eg, 0.98 for the 3XF8W), supporting adequate power. Although underpowered to detect a meaningful difference in the bilateral group, 16 subjects is in line with other gait studies that have published data on 10 [13], 15 [14], or 19 [15] subjects with bilateral amputations, a challenging population to recruit and enroll. The study is also powered (81%) to detect a 75% preference for one configuration (vs 50% under the null) using a sign test with n=30. Although no minimal clinically important difference has been established, it is predicted that a standardized effect of at least 0.50 will correspond to an impactful improvement in participants’ physical function.

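### The Objective raises whether amputation groups respond differently, but the rule that every analysis is run within group leaves no planned comparison of the configuration effect between groups

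*Protocol article*

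**What the plan says.** - **Primary objective** (Abstract, Background). It opens "The primary objective of this study is to investigate whether a novel prosthetic foot with a polycentric ankle" and goes on to ask whether this foot improves mobility and daily performance in three listed populations: unilateral above-knee, unilateral below-knee at K2, and bilateral.
- **Objective** (Abstract). After a sentence about understanding the functional impact of the foot, it adds that "it is unknown whether people with different amputations and mobility levels respond differently".
- **Methods** (Abstract). Having noted benefit in highly active users, it says "this study aims to evaluate the impact on individuals with more significant mobility limitations".
- **Statistical Analysis.** "The primary analysis will compare the META Arc foot in locked versus unlocked configurations". The section ends with the rule "All analyses will be performed separately for each group".
- **Primary Outcomes.** Three performance tests are analysed jointly: "a multivariate analysis of variance (MANOVA) will be used to evaluate the effect of foot configuration at α=.05", with paired tests on each outcome only if the multivariate test is significant.
- **Power.** For the two larger groups the section says "With n=30 for the above-knee and K2 groups, the study is powered (>80%) to detect a standardized effect size of 0.53". Its figure for the smallest group is lower: "In the bilateral group (n=16), the power is greater than 50% for the same effect size". The section concedes that the bilateral group is underpowered, and it cites a larger preliminary effect of 0.98 for one outcome (3XF8W).

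The sections on primary, satisfaction, secondary, logbook and walkway data describe no comparison between groups and no group-by-configuration term.

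**The concern.** Three within-group tests give three answers to whether the foot works in a given group. None of them answers whether it works differently in one group than in another. That second question needs an estimate of the difference between group-specific effects, and the word *All* in the analysis rule leaves no room for one.

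The gap matters because the groups have unequal power. A significant result in above-knee users beside a non-significant one in bilateral users could be taken as a difference in response when it reflects only 30 participants against 16. The article expects its results to guide prescription and inform reimbursement, so such a misreading could affect which users are offered the foot.

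**Working it through.** **Inputs.** From Power: n = 30 (above-knee), 30 (K2) and 16 (bilateral), with standardized effects of 0.53 (planning), 0.50 (judged impactful) and 0.98 (preliminary, one outcome). From Primary Outcomes: α = 0.05. Assumed: two-sided tests (sidedness is not stated), independent groups and, for between-group contrasts, a common SD of the locked-unlocked change.

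**1. Reproduce the stated power.** For a paired t test the noncentrality is d√n on n − 1 degrees of freedom.
- n = 30: 0.53 × √30 = 2.90, power 80.1% (stated: above 80%).
- n = 16: 0.53 × √16 = 2.12, power 50.9% (stated: above 50%).

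Both agree with the article. A normal approximation (82.7%, 56.4%) and a one-sided test (88.3%, 64.7%) also satisfy the stated bounds, but the two-sided t test is the closest match.

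**2. Chance of discordant verdicts when the true effect is identical in all groups** (single paired t test, d = 0.53).
- All three significant: 0.801 × 0.801 × 0.509 = 0.327.
- None significant: 0.199 × 0.199 × 0.491 = 0.019.
- Mixed: 1 − 0.327 − 0.019 = 0.654.

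Pairwise:
- A group of 30 significant and the bilateral group not: 0.801 × 0.491 = 0.393. Discordant in either direction: 0.494.
- Above-knee against K2: 2 × 0.801 × 0.199 = 0.319.

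**3. Sensitivity to the true effect** (same method).

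| d | Power, n = 30 | Power, n = 16 | Mixed verdicts |
|---|---|---|---|
| 0.50 | 75.4% | 46.5% | 70.3% |
| 0.53 | 80.1% | 50.9% | 65.4% |
| 0.98 | 99.9% | 95.5% | 4.6% |

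**4. Under the planned multivariate test.** For the within-person contrast, MANOVA on three outcomes is a Hotelling test. Its power depends on the correlation ρ among the outcome changes, which the article does not give. With d = 0.53 on all three outcomes:

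| ρ | Power, n = 30 | Power, n = 16 | Mixed verdicts |
|---|---|---|---|
| 0 | 98.4% | 75.9% | 1 − 0.984² × 0.759 − 0.016² × 0.241 = 27% |
| 0.5 | 80.1% | 44.2% | 1 − 0.801² × 0.442 − 0.199² × 0.558 = 69% |
| 0.8 | 67.9% | 34.8% | 1 − 0.679² × 0.348 − 0.321² × 0.652 = 77% |

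The power gap between groups remains at every ρ tried. The chance of mixed verdicts varies widely.

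**5. What a direct comparison could detect.** The standard error of a between-group difference, in SD units of change, is √(1/n₁ + 1/n₂).
- 30 vs 30: SE = 0.258. Power for a 0.53 SD difference is 52.3%. The difference detectable with 80% power is 0.74 SD.
- 30 vs 16: SE = 0.310. Power for 0.53 SD is 38.8%. The difference detectable with 80% power is 0.89 SD.
- Three-group F test with one group differing by 0.53 SD: power 36.0% if it is the bilateral group, 49.5% if it is a group of 30.

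**The case against.** The strongest defence is that the trial does not set out to compare groups. The primary objective, the secondary aim (unlocked against usual foot) and the hypotheses in the Discussion all concern benefit from the foot, and separate analyses answer them. The sentence in the Objective names an unknown and specifies no comparison. Next to the Abstract's remark about highly active users, it could even mean differently from those users. This largely stands. A reader might infer that the primary objective cannot be answered, and the document does not support that. It also does not remove the gap: read literally, the sentence is about different amputations and mobility levels, which is how the three groups are defined.

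A reader might also infer that the investigators will treat differing significance as differing response. No text says so. Only the possibility of that misreading can be argued.

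A third defence is that a condensed article may leave an exploratory interaction to the full plan, and that published group means and SDs would let anyone compute the differences. The second half is fair, so it would be too strong to say that the data can never answer the question. The first half is weak, because the article states a positive rule covering all analyses and so goes beyond leaving a detail out.

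Finally, declining to pool clinically distinct populations is a defensible choice, and the low bilateral power is openly disclosed. That stands, and the point does not depend on pooling. Nor does the 65% figure hold generally: it applies to a single paired t test at 0.53, falls to 4.6% at 0.98, and ranges from about 27% to 77% for the planned multivariate test.

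**Conclusion.** The point holds in a limited form. The Objective raises possible differential response, the analysis rule excludes the comparison that would address it, and unequal power makes discordant verdicts a real prospect even when the effect is the same in every group. At the planning effect of 0.53 the chance of discordance is about 65% for a single paired t test and roughly 27% to 77% for the MANOVA. At 0.98 it is about 5%. Differing significance across groups would therefore be poor evidence of differing response near the effect on which the trial was sized.

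These figures assume two-sided tests, independent groups and an identical standardized effect in each group. The MANOVA range further assumes 0.53 on all three outcomes with a common correlation between 0 and 0.8. The primary within-group conclusions are not undermined. This is a gap worth closing in the plan, and it is not a flaw in the primary analysis.

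**What to change.** 1. Keep the group-specific primary tests unchanged.
2. Amend the rule in Statistical Analysis so that it covers the primary tests, and add one prespecified exploratory mixed model per primary outcome over all participants: configuration, period, group and configuration by group, a random participant effect, and residual variances that may differ by group.
3. Report the between-group differences in configuration effect with 95% confidence intervals.
4. State that the separate tests do not compare groups, and that any claim of differing response rests on these estimates and not on one group being significant while another is not.
5. Make the change before the condition labels are unblinded.

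A pooled configuration effect is optional. With 76 participants it would have more than 99% power at 0.53, or 80% power at 0.33, but only if one common effect and a common SD of change are assumed. It should be labelled accordingly if used.

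The cost is three extra models and a few sentences, with no new data. The drawback is imprecision: 80% power only for differences of about 0.74 SD (30 vs 30) or 0.89 SD (30 vs 16). A non-significant interaction must therefore not be presented as evidence that the groups respond alike.

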### Primary Outcomes

Primary performance outcomes include the TUG, the 3XF8W, and the Four Square Step Test. Assumptions of normality and homogeneity will be tested. If met, a multivariate analysis of variance (MANOVA) will be used to evaluate the effect of foot configuration at α=.05. A permutational MANOVA will be used if assumptions are violated. If multivariate differences are significant, post hoc paired *t* tests (or Wilcoxon signed-rank tests if nonnormality is present) will be used to assess individual outcomes without correction for multiple comparisons. In order to help control the familywise type I error risk, pairwise comparisons of the primary outcomes will only occur if the multivariate difference comparison from the MANOVA is significant.

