The study populations are particularly relevant to veterans and service members with amputations resulting from combat-related trauma or disease. Prosthesis users should be challenged to move sideways, move backward, and turn. Biomechanical components are often conflated with typical summary scores, which are typically based on the time it takes to complete a task. By conducting component analysis, mobility challenges, prosthetic design, and training can be addressed to better fit the needs of the users.

There are some limitations to the protocol. The participants have a 2-week accommodation period for each phase of the A1-B1-B2-A2 crossover design. There is no structured training program. Although the order of locked and unlocked use of the study foot will be varied between individuals, participants may continue to become more accustomed to using the foot into the next period, with the possibility of bias in the results.

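### The primary crossover comparison has no period term, although the article says adaptation may continue into the second period; adjusting for order is a cheap improvement

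*Protocol article*

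**What the plan says.** The Study Procedures section describes an A1-B1-B2-A2 sequence in which the order of the two B conditions (locked, unlocked) is randomised. The Randomization section stratifies the blocks by study site only. Statistical Analysis makes locked versus unlocked the primary comparison and runs every analysis separately in the three amputation groups. It blinds the statisticians to the labels but works "with knowledge of the order (X→Y or Y→X").

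Under Primary Outcomes, "a multivariate analysis of variance (MANOVA) will be used to evaluate the effect of foot configuration at α=.05" for the TUG, the figure-of-eight test and the Four Square Step Test. Also: "Assumptions of normality and homogeneity will be tested", and "A permutational MANOVA will be used if assumptions are violated". If the multivariate test is significant, "post hoc paired *t* tests (or Wilcoxon signed-rank tests if nonnormality is present) will be used to assess individual outcomes". Foot configuration is the only factor named.

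The limitations paragraph in the Discussion (under Expected Findings) says that "participants may continue to become more accustomed to using the foot into the next period, with the possibility of bias in the results". The only order-related analysis is of carryover. It appears under Secondary Outcomes and leads to sensitivity analyses.

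**The concern.** If people keep getting used to the study foot, period 2 results differ from period 1 results whichever configuration is worn. That shift enters the X−Y difference with one sign in order X→Y and the opposite sign in order Y→X. An analysis that ignores order then does one of two things. With equal orders, the shift cancels from the mean but inflates the variance, so power is lost. With unequal orders, part of the shift stays in the mean and is read as an effect of the foot.

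Blocking by site does not balance order within an amputation group, which is the unit of analysis. The exposure is largest in the bilateral group, where n is 16 and power is already low. The multivariate test is also the gate to the individual outcomes, so power lost there is lost for all three.

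**Working it through.** **Inputs from the article.** Effect 0.53; n=30 (above-knee, K2) and n=16 (bilateral); α=.05, taken as two-sided because sidedness is not stated.

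**Assumed, because the article gives no figure.** Period shift π from 0 to 1.0, in SDs of the within-person difference; order splits within a group; for the multivariate check, a correlation of 0.5 between outcomes, with the same effect and shift on all three.

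**Step 1: the article's own power.** It states "With n=30 for the above-knee and K2 groups, the study is powered (>80%) to detect a standardized effect size of 0.53" and "In the bilateral group (n=16), the power is greater than 50% for the same effect size". A paired t test (noncentral t, noncentrality 0.53√n) gives 80.1% at n=30 and 50.9% at n=16. Both are reproduced, for a paired test with no period shift.

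**Step 2: model.** For each participant D = τ + πs + e, where D is the X−Y difference, s = ±1 codes order and e has SD 1.

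**Step 3: balanced orders.** The mean of D is still τ, but the expected sample variance becomes 1 + π²·n/(n−1). Approximate power is P(Z > t_crit·√[1 + π²n/(n−1)] − 0.53√n). At n=30, t_crit = 2.045 and 0.53√30 = 2.903.
- π=0.5: √(1 + 0.25×30/29) = 1.122; 2.045×1.122 − 2.903 = −0.61; power about 73%.
- π=1.0: √(1 + 30/29) = 1.426; 2.045×1.426 − 2.903 = 0.01; power about 50%.

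Simulation agrees:

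| Setting | π=0 | 0.25 | 0.5 | 1.0 |
|---|---|---|---|---|
| n=30 (15:15), paired t | 80% | 78–79% | 73% | 50% |
| n=30 (15:15), order-adjusted | 80% | 80% | 80% | 80% |
| n=16 (8:8), paired t | 51% | 48% | 41% | 21% |
| n=16 (8:8), order-adjusted | 50–51% | 50–51% | 50–51% | 50–51% |

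For the three-outcome within-person test at n=30, power is about 66% unadjusted against 80% adjusted at π=0.5, and about 33% against 80% at π=1.0.

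**Step 4: uneven orders.** Conditional bias = π(n1−n2)/n.
- 11:5 of 16, π=0.5: 0.5×6/16 = 0.19 SD, which is 0.1875/0.53 = 35% of the planned effect. Unadjusted power is 19% or 69%, depending on the direction of the split; adjusted power is 45% either way.
- 18:12 of 30, π=0.5: 0.5×6/30 = 0.10 SD.
- 20:10 of 30, no true effect: conditional type I error is 10% at π=0.5 and 17–18% at π=1.0, against 5% adjusted.

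**Step 5: how likely such splits are.** If order within a group behaves like a coin toss, 11:5 or worse in 16 has probability 2×P(Bin(16, ½) ≥ 11) = 21%. For 30, 18:12 or worse has 36% and 20:10 or worse 10%. If order were exactly balanced over the planned total (30+30+16 = 76) and groups fell at random within it, the hypergeometric figures would be 16%, 24% and 3%. The coin toss is thus the less favourable of the two assumptions.

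**Step 6: average over the randomisation.** With order assigned by coin toss, the unadjusted estimate is unbiased. Type I error of the paired t test stays at 5% for π = 0, 0.5 and 1.0 at both sample sizes.

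**The case against.** Several counter-arguments have force.

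- **Randomised order protects validity.** This stands. Over the randomisation there is no bias and type I error is 5%; with balanced orders the unadjusted test is conservative (about 3% at π=0.5). The bias and 10% error figures apply only to particular uneven splits, and the actual splits are unknown.
- **The shift is hypothetical.** This stands too. The article says adaptation may continue, not that it is expected, and gives no size. At 0.25 SD the loss is only about 2 points at n=30 and 3 at n=16. A shift of 1.0 SD would be nearly twice the effect the trial is powered for.
- **An article leaves model terms to the SAP.** This holds in part. Much detail is rightly left there, but the Primary Outcomes section already fixes the test, the assumption checks, the fallback, the follow-up tests and the gate. An SAP that followed it as written would omit period.
- **Order is already dealt with under carryover.** It is not. Carryover is a different quantity from a shift common to both orders, and it reaches only sensitivity analyses.

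A reader might go further and infer, from the homogeneity check and the plain term MANOVA, that the two configurations will be analysed as independent groups. The article does not support that. The follow-up tests are explicitly paired. The stated power matches a paired test; independent groups at 0.53 would give 52.3% and 30.6%. What is fair to say is that neither the within-participant form of the MANOVA nor the permutation scheme is written down.

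**Conclusion.** The point holds as a worthwhile, low-cost improvement, not as a flaw that invalidates the primary analysis. The article names possible adaptation into the second period as a source of bias, gives its statisticians the order, and then fixes a primary analysis that does not use it. At an assumed shift of 0.5 SD with balanced orders, this costs about 7 points of power at n=30 (80% to 73%) and about 9 at n=16 (50% to 41%). With an 11:5 split of 16 it displaces the estimate by 0.19 SD, and a split that uneven has a probability of about 21% under a coin toss. All of these sizes rest on assumed shifts and splits. If there is no period shift, nothing is lost by the present plan.

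**What to change.** In Primary Outcomes:

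1. State that the multivariate test is within-participant. Regress the three X−Y differences on an order code and test the intercept vector with Hotelling's T-squared. Fix the code at +1/−1 and do not re-centre it at the sample mean, because that would return the unadjusted mean difference.
2. For the permutational version, restrict permutations to within participant and have them respect sequence.
3. Replace the follow-up paired tests with period-adjusted crossover contrasts (half the sum of the two order-specific mean differences).
4. Report the order split in each amputation group.

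The cost is wording, a little code and one degree of freedom per group. With equal orders and no shift, power is practically unchanged (80.1% to 80.0% at n=30). With uneven orders and no shift there is a real but modest price: 80% to 75% at 20:10, and 51% to 45% at 11:5 of 16. No new data are needed. Blinding is kept, because the statisticians already hold the order without the labels. A period term does not remove differential carryover, which should stay in the sensitivity analyses.

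### A pretest on the trial data picks the primary multivariate test separately in each amputation group, and the two candidate tests are not interchangeable

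*Protocol article*

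**What the plan says.** All places are in the Methods of the protocol article.

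- **Primary Outcomes**, the endpoints: "Primary performance outcomes include the TUG, the 3XF8W, and the Four Square Step Test". The Physical Performance Measures section shows that these are timed tests.
- **Primary Outcomes**, the choice of test: "Assumptions of normality and homogeneity will be tested". If they are met, "a multivariate analysis of variance (MANOVA) will be used to evaluate the effect of foot configuration at α=.05". If not: "A permutational MANOVA will be used if assumptions are violated".
- **Primary Outcomes**, the follow-up tests: "pairwise comparisons of the primary outcomes will only occur if the multivariate difference comparison from the MANOVA is significant".
- **Statistical Analysis**: "All analyses will be performed separately for each group".
- **Power**: "With n=30 for the above-knee and K2 groups, the study is powered (>80%) to detect a standardized effect size of 0.53". The bilateral group has n=16, with power above 50% for the same effect.

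The article names no pretest and no threshold. For the fallback it gives no distance, scaling or permutation scheme. It gives no SDs or correlations for the three tests.

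**The concern.** Three features of the stated rule are unhelpful whatever a fuller analysis plan adds.

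1. **The data choose the test.** A pretest rejects by chance even when its assumption is true. With three separate analyses, the groups can be judged by different primary tests for no substantive reason.
2. **One of the two pretests appears to miss the point.** Each participant supplies both a locked and an unlocked result, and the follow-up tests are paired. The comparison rests on the within-person differences. Their variance is the locked variance plus the unlocked variance minus twice the covariance, and nothing requires the first two to be equal. A check of equal spread across configurations could trigger the switch without cause.
3. **The two tests can weigh the outcomes differently.** MANOVA gives the same answer in any units. A permutational MANOVA built on distances does not, unless the outcomes are first put on a common scale.

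Individual outcomes are examined only after a significant multivariate result. If one outcome dominates the fallback, a real effect on the other two primary outcomes could go untested.

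**Working it through.** **Inputs.** From the article: three outcomes, α=.05, groups of 30, 30 and 16, standardized effect 0.53. Assumed, because the article gives no figure: Shapiro-Wilk at .05 on each of the three differences; correlation r=0.3 between differences; SD of the 3XF8W difference equal to k times that of TUG and Four Square, with k from 1 to 4; and, for the fallback, Euclidean distance on unscaled seconds with sign flips within person.

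**1. The article's own power figures.** For a two-sided paired t test the noncentrality is 0.53 × √n.
- n=30: 0.53 × √30 = 2.90 on 29 df, power 80.1%
- n=16: 0.53 × √16 = 2.12 on 15 df, power 50.9%

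Both match the stated values. They describe a test of one outcome, which is neither branch of the multivariate rule.

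**2. How often the switch happens by chance.** With normal differences and independent checks, the rate is 1 − 0.95³ = 14.3% per group. Simulation at r=0.3 gave 13% to 16%. The chance that the three groups do not all get the same test:
- at 14% in every group: 1 − (0.14³ + 0.86³) = 1 − (0.003 + 0.636) = 36%
- at simulated rates of 15.5% (n=30, two groups) and 14.4% (n=16): 1 − (0.155² × 0.144 + 0.845² × 0.856) = 1 − (0.003 + 0.611) = 39%

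With heavier tails (t with 5 df), simulated rates of 55.5% and 38.5% give 1 − (0.555² × 0.385 + 0.445² × 0.615) = 76%. For assumed lognormal times, the switch rate per group was 29% to 64%.

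**3. Why the branches differ.** Within-person MANOVA is Hotelling's T² = n·d̄ᵀS⁻¹d̄, which is free of units. Sign flips leave the total sum of squares unchanged, so the Euclidean fallback amounts to n·Σd̄ⱼ². Take the SD of the TUG and Four Square differences as 1. Effects of 0.53 on those two then add 2 × 30 × 0.53² = 16.9 at n=30. The 3XF8W term is pure noise, with mean k² and SD about √2·k².

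| k | 3XF8W noise: mean (SD) | fallback power, n=30 | fallback power, n=16 |
|---|---|---|---|
| 1 | 1 (1.4) | 88-91% | about 60% |
| 2 | 4 (5.7) | 56-59% | 30% |
| 3 | 9 (12.7) | 22-24% | 12-13% |
| 4 | 16 (22.6) | 10-12% | 8% |

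The ranges are across separate simulations of 1,000 or more data sets.

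For Hotelling, λ = n·δᵀR⁻¹δ with R⁻¹ = (I − 0.1875·J)/0.7, where J is the all-ones matrix and 0.1875 = 0.3/1.6. With δ = (0.53, 0, 0.53) this is n × (0.5618 − 0.1875 × 1.1236)/0.7 = 0.5016·n, or 15.0 at n=30 and 8.0 at n=16. The noncentral F on 3 and n−3 df gives 87% and 52% at every k (simulated 85-89% at n=30).

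**4. The whole two-stage rule at k=3.** With normal differences the fallback is used in only some data sets. At n=30: 0.870 − 0.150 × (0.870 − 0.235) = 77.5% (simulated 78%). At n=16: 0.521 − 0.129 × (0.521 − 0.132) = 47% (simulated 47%). With t (5 df) differences, simulated power was 54% against 88% for Hotelling at n=30, and 45% against 61% at n=16.

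**5. Cases that go the other way (k=3, r=0.3).**
- Effect on 3XF8W only: raw fallback 78% against Hotelling 68% (n=30), and about 50% against 35% (n=16). At r=0.5 and n=30 the order reverses slightly (77% against about 80%).
- Effect of 0.53 on all three: 88% against 89% (n=30), and 59% against 54% (n=16).
- No effect: the two-stage rule rejected in 4.1% to 4.9% of data sets.

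**The case against.** A reader might infer that the fallback runs on seconds and is driven by the longest test, so that TUG and Four Square effects will be missed. The article does not support this. It states neither distance nor scaling, and a condensed article may leave both to a fuller plan. Duration is not the driver either: what matters is the SD of the within-person difference, which the article does not give. With equal SDs nothing is lost.

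The harmful scenario also runs against the article's expectations. The Power section cites a preliminary effect of 0.98 on the 3XF8W, and Expected Findings predicts improvement on that test. If all three outcomes improve, or only the 3XF8W does, the rule loses little or even gains.

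Type I error is held, the rule is written in advance, the statisticians are blinded to condition labels, and no comparison between groups is planned in the analysis sections. Different tests by group therefore invalidate no stated comparison. Nor does the article say across what homogeneity is tested, so reading it as locked against unlocked is an interpretation.

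All of this limits the size of the point. It does not remove the rule itself: the text says that a pretest on the trial data selects the primary test, group by group. A fuller plan could undo that only by departing from the article.

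**Conclusion.** The point holds in a limited form. The data-driven choice of primary test is stated in the article. The chance of switching rests on an assumed pretest: about 14% per group with exactly normal differences, and more with skewed or heavy-tailed times. Homogeneity between the two configurations is not needed for a within-person comparison.

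The loss of power is conditional. It needs an unscaled Euclidean distance, a 3XF8W difference that varies more than the other two, and effects confined to TUG and Four Square. Under those assumptions the rule for follow-up tests would block separate examination of two named primary outcomes. The harm is an unstable choice of test and possible loss of power, not inflation of type I error. The change is worth making because it costs almost nothing.

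**What to change.** Delete the pretest and the switch, and name one within-person test for all three groups. A suitable choice is Hotelling's T² on the three within-person differences with a sign-flip permutation p-value. It needs no normality, only differences that are symmetric about zero under the null. A log scale for the times is optional.

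If permutational MANOVA is kept, use it in every group and state three things: the distance, the scaling and the permutation scheme. Standardise each outcome's within-person difference by a scale that sign flips do not change (its root mean square), or recompute the scale in each permutation. Permute within person only. With standardised differences, power in the scenario above is close to 90% at n=30 at every SD ratio.

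Cost: a few sentences in the analysis section and no new data. Data collection is expected to run to March 2027 and the statisticians are blinded to condition labels, so it can be done before unmasking. The downside is a small loss if only the 3XF8W changes. At k=3, r=0.3 and n=30, Hotelling gives up about 10 points to a raw-seconds fallback that is always used. Against the two-stage rule with 15% switching, that is about 0.15 × 10 = 1.5 points.
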